## Trial design

The hybrid type 3 implementation-effectiveness design [1, 2, 53] was selected because it primarily focuses on comparing different implementation methods. Randomization is at providers’ level, and the patient intervention is the same across the three facilitation conditions. This type of trial is uniquely suited to accelerate the transition of technology-supported EB-BSM practices tested in clinical research settings into real clinical and operational environments with ADSMs with chronic insomnia disorder and stress-related sleep disturbances. The proposed implementation-effectiveness hybrid design will yield insights into the most cost-effective strategies for implementing the COAST platform in MTFs, affiliated clinics, and wellness centers. The study can thus provide useful information to stakeholders (e.g., directors, administrators, other decision-makers) in evaluating the full potential of COAST to support access to and delivery of EB-BSM practices. Furthermore, this design maximizes the ecological validity and generalizability of findings.

The investigative team has well-established relationships with key decision-makers and leaders, whereby the results of this trial can be directly translated into policy mandates and best practice guidelines across the Defense Health Agency (DHA). We employ an implementation science framework to evaluate the reach, adoption, and sustainability of digital sleep therapeutics in MTFs and affiliated clinics, which are expected to readily translate to broader veteran and civilian healthcare settings. The overall study design is summarized in Fig. 1.

**Fig. 1 Fig1:**
[figure not shown]
Design of the hybrid type 3 implementation-effectiveness trial

## Trial status

This study received ethics review and approval from Solutions, IRB (Protocol #2019/12/10) on January 29, 2020; from the Naval Health Research Center (NHRC) on April 28, 2020 (Protocol #: NHRC.2019.0018); and from the US Army Medical Research and Development Command (USAMRDC), Office of Research Protections (ORP), Human Research Protection Office (HRPO) (HRPO Log Numbers E01442.1a [NOCTEM, LLC], E01442.1b [NHRC], E01442.1e [Naval Medical Center, San Diego], and E01442.1f [Naval Hospital Camp Pendleton]) on September 11, 2020.

## NOCTEM Clinician-Operated Assistive Sleep Technology (COAST™) platform

The NOCTEM COAST platform is designed to enhance the scalability of EB-BSM practices. Briefly, COAST is a software that encompasses clinician-centered dHealth clinical decision support algorithms and tools, a patient app, and a secure text messaging system. COAST is a cross-platform system that runs on any smart device (Android, iOS, Windows, etc.). Proprietary algorithms utilize self-report data collected daily from patients to identify disordered sleep patterns, which then guide personalized recommendations for intervention to the clinician. Sleep disturbances consistent with insomnia, nightmares, racing thoughts, daytime fatigue, sleepiness, and circadian disturbances can be detected, and evidence-based recommendations for behavioral sleep modifications are suggested to the clinicians, who then push the recommendations to the patient. The COAST tools were refined through iterative development and testing with end users, providers, and other key stakeholders in the DHA. COAST leverages patients’ preference for dHealth-based treatment approaches [54, 55], promotes engagement in treatment [56], and reduces the burdensome requirements of traditional CBTI by bringing the tools and clinical expertise directly to their smart device. These drivers also align directly with the DoD’s recognition of the unique capabilities of dHealth technologies in providing healthcare to ADSMs [57].

## Objective, aims, and hypotheses

The overarching objective of this investigation is to compare and evaluate three facilitation strategies for implementation (i.e., no facilitation, external facilitation only, and external plus internal facilitation) of the NOCTEM COAST™ platform in MTFs and clinics with a representative sample of ADSMs with common comorbid disorders. The specific aims are to (1) examine and compare the reach, adoption, sustainability, and magnitude of changes in a patient’s sleep for a new patient- and clinician-centered digital platform (COAST) alone, compared to COAST plus external facilitation (COAST+EF) or COAST plus EF and internal facilitation (COAST+EF/IF) in MTFs and affiliated clinics, and (2) quantify the magnitude of improvements in insomnia for patients who receive behavioral sleep care via the COAST platform.

Our first hypothesis is that providers randomized to the COAST+EF or COAST+EF/IF conditions will show greater (a) reach, (b) adoption, and (c) maintenance (sustainability) at 3- and 12-month follow-ups compared to providers randomized to the COAST-only condition. Our second hypothesis is that (a) COAST+EF and COAST+EF/IF will yield greater improvements in insomnia than COAST only over the acute 6-week intervention period, and (b) COAST+EF will not be inferior to COAST+EF/IF as measured by changes on the ISI over the acute 6-week intervention period.

To test these hypotheses, we will enroll at least 24 providers and 864 patients presenting with insomnia who are currently being seen at MTFs, affiliated clinics, and wellness centers across military branches. For an ecologically valid assessment of COAST’s potential to be implemented across facilities of the DHA, we will enroll providers who deliver services to ADSMs with comorbid PTSD, traumatic brain injury (TBI), chronic pain, and other psychiatric and medical conditions that are often comorbid with sleep disorders. The comparison of the three implementation strategies will provide insights into the advantages and disadvantages of each relative to patient- and clinician-centered outcomes. The results will inform anticipated larger implementation efforts across different clinical and operational settings within and outside the DHA.

## Selection criteria and enrollment of participating providers and patients

The trial aims to recruit at least 24 providers (clinicians and health coaches) who currently provide services in behavioral health to service members, their dependents, and beneficiaries across Navy Medical Forces Pacific (NMFP). The participating military treatment facilities (MTFs) and affiliated clinics are all located in Southern California. We aim to enroll providers who already deliver cognitive-behavioral health interventions as part of their regular practices, including behavioral sleep interventions like CBTI.

Each participating provider will enroll at least 36 patients over the course of 12 months, for a total minimum patient sample of 864. Across participating sites, providers will be informed of the trial through emails, newsletters, flyers, word of mouth, notifications sent to and by clinic leaders and/or department administrators, and flyers posted around the facilities and clinics. Providers will also be invited to participate in two remote half-day training workshops for which continuing education credits will be offered. The first segment of the training will be open to all interested providers at each site and focused on principles and practices of BSM.

Among providers who complete the first segment of the training, those who wish to participate in the trial will be invited to join the second segment of the training for a hands-on workshop on how to use the COAST platform. All interested providers will be eligible to enroll in the trial as long as they completed the first half of the workshop (or similar workshop in the past 6 months), evaluate and/or treat patients with insomnia, use cognitive-behavioral treatments as part of their practice, and provide electronic informed consent to participate in the trial. Providers from various backgrounds (e.g., clinical psychology, counseling, physician assistants, social work, physicians, nurses) will be eligible. We elected to enroll all eligible and interested credentialed providers, with at least a masters’ degree and training in the cognitive-behavioral therapeutic approach, and who are currently delivering care to military service members in general or specialized behavioral health clinics (e.g., concussion care clinics, pain management clinics, depression/anxiety treatment programs, sleep medicine clinic) to enroll a representative sample of providers across MTFs. Information regarding years of experience in behavioral health, experience in behavioral sleep medicine, professional degree, and clinical certification(s), as well as expectations about the use of technology in clinical settings will be collected at the onset of the study for all participating clinicians. While the study is not powered for definitive determination of the effects of each of these variables on implementation measures or patient outcomes, planned exploratory analyses will inform future implementation trials.

Prior to the COAST training workshop, all registered providers will receive an electronic copy of the consent to read and review before the training session. They will be encouraged to reach out to the study investigators or coordinators if they have questions. The consent form will be reviewed at the beginning of the COAST training workshop and questions will be addressed. Providers who decline to participate at that time will not be able to access the clinician portal nor use the COAST platform with their patients. Providers who elect to participate in the trial will provide consent by initializing each page and electronically signing the electronic consent form. A copy of the completed consent form is stored on the portal and can be downloaded by the provider. After obtaining informed consent to participate in the trial, information about providers’ background, current title, years of experience, familiarity with BSM and CBTI, and use of and proficiency with digital health tools will be collected.

During this workshop, and after, participating providers will receive access to the COAST clinician portal. During this segment of the workshop, providers will learn how to navigate both the COAST clinician portal and the patient NOCTEM app. After completing the training, providers will engage in a familiarization period with the clinician portal and app. Specifically, providers will be asked to use the COAST portal and app for a period of 10 to 14 days to become proficient with the COAST tools and workflow. During this trial period, the NOCTEM team will supervise providers’ use of the clinician portal and app. The NOCTEM team will offer consults, as needed, on the providers’ use of COAST and algorithm-driven recommendations, as well as address or communicate any technical issue that may arise during this time.

Once participating providers are familiar with the COAST platform, they will begin enrollment of eligible participants. Patients who are deemed eligible to use the NOCTEM app by their provider to support the management of insomnia and other behavioral sleep disturbances will be informed of the study. Clinicians who are investigators on the study or the assigned research coordinator will be able to enroll patients who express interest in using the NOCTEM app. Research coordinators and investigators who obtain consent from patients will follow a written script. The script follows the same structure as the electronic consent embedded in the NOCTEM COAST app. Following the script and electronic consent, the research staff member will review the study aims, procedures, risks, and alternatives prior to obtaining consent. Electronic consent will be obtained from patients via the app. For this, a waiver for documentation of consent has been granted. The research staff will then contact the treating clinician and inform him/her/them that their patient agreed to participate in the research study, is registered onto the clinician’s NOCTEM COAST portal, and is utilizing the app.

The sleep intervention will be delivered via the COAST digital sleep health platform to all participating patients. Exclusion criteria for participants are restricted to untreated sleep apnea [including less than 4 h of positive airway pressure (PAP) therapy per night]), currently pregnant or breast-feeding, parent of a newborn child, or a diagnosis of bipolar or psychotic disorders. The limited scope of exclusion criteria intends to optimize the generalizability of findings and representativeness of the sample relative to the larger population of ADSMs, veterans, and beneficiaries who receive care in MTFs and affiliated clinics of Navy Medical Forces Pacific. Participants who report clinically significant sleep disturbances despite concurrent pharmacological treatment with sedatives of hypnotics will be eligible for enrollment in the study if their provider deems it appropriate; discontinuation of medications is not required. There shall be no exclusion based on sex, minority status, or other health-related status (other than listed above). These exclusion criteria will be recommended to providers to avoid exacerbating excessive daytime sleepiness (for sleep apnea and/or pregnant women and new parents) and exacerbation of symptoms (for psychotic or bipolar disorders). Providers may also elect not to use the COAST platform, and refer a patient to primary care, psychiatry, sleep medicine, or another specialty care clinic for pharmacological sleep treatments if they deem it necessary for the patients. The ultimate decision regarding the inclusion of any patient will be left to their clinician, as s/he has the necessary clinical information to determine the best course of action for a given patient.

For patient enrollment, consent is obtained electronically via the NOCTEM app prior to activating the app. Electronic consent is an appropriate method for the present project because (1) COAST is a minimal risk care-enhancement project, (2) no protected health information (PHI) is stored on the app, and (3) no identifiable information will be collected via the portal or the app. After obtaining consent, patients will gain access to the patient app, including an orientation by the research team member provider on how to use the app and its assessment and messaging features. They will also be instructed to contact their provider via the secure text messaging system or by phone if they have any questions. No identifiable information will be visible on the patient app or clinician portal.

## Randomization of providers

After completing the COAST training and 10- to 14-day familiarization period, providers will be randomized in a 1:1:1 manner to one of three implementation strategies: COAST only, COAST+EF, or COAST+EF/IF (implementation strategies are further described below). Providers will be randomized within participating sites to one of the three facilitation conditions. A computer-generated randomization schedule based on a permuted block design will be created a priori. Using a permuted block design ensures that there will be equal numbers in each arm. The allocation will follow the generated sequence and the local research point of contact will inform the providers of their assignment at the end of the familiarization period, prior to patient enrollment.

## Intervention

Facilitation has been shown to enhance implementation of evidence-based treatments into practices [58, 59]. External facilitation (EF) refers to the addition of a key individual who is not embedded in the clinical setting, but who is tasked with supporting providers who are implementing new evidence-based practices, such as COAST in this trial. Because the external facilitator is not embedded in a single clinic, s/he may help in generating creative solutions for perceived and real barriers. Since an EF does not share clinical responsibilities and is not a supervisor or superior, s/he may also offer a supportive and guiding hand and be less hesitant to address difficult situations. This individual is available to troubleshoot as issues or questions arise and provide more interactive support, consultation, and feedback to providers. For the project, the NOCTEM team will provide EF via bi-weekly consult or supervision teleconference, or via telephone. The EF team will also be available by email and text messaging on an as-needed basis.

Internal facilitation (IF) refers to the presence of a champion embedded in the local system or clinic in which the evidence-based practice is being implemented, and who can serve as a more proximal facilitator in addition to the external facilitation. Compared to EF, IF has the advantage of providing a key resource who has a proximal relationship with providers and local administration, and who has in-depth knowledge of a clinic’s unique context, operational intricacies, clientele, etc. For the proposed trial, local sleep experts will provide IF; however, the IF will not be a study clinician. The comparison of the three implementation strategies will provide insights into the advantages and disadvantages of each of these three implementation interventions relative to patient-, clinician-, and system-level outcomes. The results will inform anticipated larger implementation efforts across different clinical and operational settings.

Prior to the enrollment of providers and patients, the NOCTEM team and the EFs and IFs will first complete an in-depth review of written guidelines and standard operating procedures for this project. During the trial, the EF and IF teams will meet monthly by phone and communicate via email, as needed, between scheduled monthly meetings to address any issues that arise and share newly acquired information. The EF and IF guidelines will be updated as needed to make sure both processes are documented and kept up to date during the trial.

The sleep intervention is the same for all patients enrolled by participating clinicians. When a disordered sleep pattern is detected by the NOCTEM algorithms (usually within 7 days), the provider will receive automated sleep recommendations for each patient and will be asked to review and confirm prior to forwarding it to the patient. Recommendations are consistent with stimulus control, sleep restriction, and other EB-BSM techniques, including suggested times for rise time and bedtime and exercise to minimize nightmares. Providers may elect to modify the algorithm-driven recommendations as they see fit, based on knowledge of their patients. Patients will receive their provider-approved, personalized behavioral sleep recommendations on a weekly basis. This process will be repeated for the next 4 to 6 weeks.

Participating patients will not be terminated from the study until (1) they decide to stop using the app; or (2) their provider deems that a different treatment or referral is required; or (3) the treatment course is complete, and the use of the app is no longer necessary; or (4) the end of the project. COAST is not commercially available, and patients who wish to remain in sleep treatment will be encouraged to discuss options with their provider. Because the COAST system requires that a provider monitors entries and sleep status and progress, the app will be disabled when a patient is no longer in the care of a provider. This will avoid misleading patients that they are still under the care of the provider through the app only.

Over the duration of the intervention, patients will be asked to complete daily sleep logs, measures of overall sleep quality, daytime psychiatric symptoms, perceived improvements, and side effects through the app. Symptoms of depression, anxiety, and PTSD will be assessed weekly with the PHQ-2 [60], GAD-2 [61], and PC-PTSD-5 [62], respectively. Side effects will be evaluated weekly using adapted version of the Asberg Side Effect Scale [63], whereas sleepiness will be assessed with the Epworth Sleepiness Scale [64, 65]. The main expected side effect is a transient increase in sleepiness. Side effect ratings from the modified Asberg Side Effect Scale and Epworth Sleepiness Scale are assessed weekly and available to providers for review to inform the titration of behavioral recommendations as needed. Self-perceived improvements will be assessed with the Patient Report Global Impression Scale [66]. Providers will be asked to complete the Clinician Global Impression Scale [66] on a weekly basis after reviewing patient-reported side effects and other symptom measures, and sleep diaries.

All data gathered in this project from providers and patients will be completed electronically, and data will be saved automatically on secure the NOCTEM cloud. Data completeness is facilitated at the time of completion by participating patients or providers by not allowing participating patient to skip questions (yet, one can decline to answer a question), and by reminders to complete incomplete forms sent via the app or portal. Automated data review and report will be generated to assess completeness and upload into the main database.

Data management, monitoring of the integrity of the interventions (i.e., facilitation conditions), training of facilitators, and local research assistants will be coordinated by the NOCTEM team. A Collaborative Research and Development Agreement (CRADA) is in place with site principal investigators so that data collected can be shared.

The NOCTEM cloud-based databases are protected by several procedures, including password protection of subject data and a firewall around the NOCTEM network. For the NOCTEM COAST platform, we have developed comprehensive privacy and security measures including unique activation personal identification numbers and passwords, secure socket layer (HTTPS/SSL) protocol, strong encryption, and compliance with the Defense Information Systems Agency (DISA) Security Technical Implementation Guides (STIG). All data are stored in a secure, HIPAA-compliant cloud server. Clinicians and participating patients will have unique research ID numbers that will be used in lieu of personally identifiable information for data collection and storage. The research ID numbers are unrelated to any potentially identifiable numerical series, such as social security number, medical record number, or date of birth. Study data will be kept strictly confidential, and participants’ identities will not be revealed in any publication.

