**Assessments:**							
Demographics and practice survey			X				
Post-training survey			X				
Organization readiness for implementing changes			X			X	X
System usability scale			X	X		X	X

Fidelity is evaluated by quantifying the adherence (or discrepancy) between algorithm-recommended interventions relative to interventions that are sent to patients by providers. As in some cases there may be valid clinical reasons why a provider determines a patient should not receive the algorithm-recommended intervention (e.g., sickness, incompatible with assigned duties), we expect a rate of non-adherence of approximately 20%—noting we will not be accessing patients medical records to validate the potential reasons for deviations.

The primary patient-centered outcome measure of treatment effectiveness is the Insomnia Severity Index (ISI [32]). Other symptom domains to be assessed are summarized in Table 3, and include the PTSD Checklist-5 (PCL-5 [47, 48]), the 8-item Patient Health Questionnaire (PHQ-8 [49]) to assess symptoms of depression, the 7-item Generalized Anxiety Disorder scale of the PHQ (GAD-7 [50]), the PEG, a 3-item validated and reliable pain measure [68], and the 4-item PROMIS Satisfaction with Social Roles and Activities [69]. For patients, the total time required to complete the battery is approximately 20 min. The battery will be completed through the NOCTEM app at baseline, post-treatment, and again 3 and 12 months post-treatment.

**Table 3 Tab3:** Self-report measures of sleep and daytime symptoms to be completed by participating patients at baseline, post-intervention, and at the follow-up assessments

Domain	Scale	Number of items	Time to complete

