## Statistical analyses plan and power calculations

Preliminary data analyses (e.g., descriptive statistics, correlations, principal component analysis) will be performed prior to hypothesis testing to check for collinearity of covariates and outcome measures, to ensure completeness and accuracy of data, and to evaluate distributions. Missing observations will be investigated to determine the underlying mechanism (missing at random, completely at random, not at random) so that appropriate methods for handling the missing data can be employed. Namely, if data are missing at random, we will use multiple imputation (MI) to ensure that any individuals with missing covariates or outcome data can be included in the analysis sample. However, if data are found to be missing not at random, we will use methods that explicitly model this type of nonrandom missingness (e.g., pattern mixture models) and perform sensitivity analyses evaluating the impact of the missingness. Power was computed using PASS statistical software and documentation. Each model will include covariates including study site, patient age and sex, military rank, and use of psychotropic medication (yes/no). Masked data will be provided to the biostatistician who will perform the analyses. Randomization will be unmasked only after analyses are finalized.

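### Patients who stop the app or are referred early have no stated route to the 6-week ISI, the app-only follow-up conflicts with the exit rules, and the missing-data rule rests on a test that cannot be made

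*Protocol article*

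**What the plan says.** Under Outcome measures, "The primary patient-centered outcome measure of treatment effectiveness is the Insomnia Severity Index". On route and timing: "The battery will be completed through the NOCTEM app at baseline, post-treatment, and again 3 and 12 months post-treatment". No other route is described.

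The Intervention section sets the ends of participation: "Participating patients will not be terminated from the study until (1) they decide to stop using the app"; or "their provider deems that a different treatment or referral is required"; or "the treatment course is complete, and the use of the app is no longer necessary"; or the project ends. It adds that "the app will be disabled when a patient is no longer in the care of a provider". On course length, once a disordered pattern has been detected (usually within 7 days): "This process will be repeated for the next 4 to 6 weeks".

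The Statistical analyses section tests hypothesis 2 on the change in ISI from baseline to 6 weeks. It assumes 36 patients per provider and reports 0.80 power for a standardized difference of 0.232. On missing data it says: "Missing observations will be investigated to determine the underlying mechanism (missing at random, completely at random, not at random". Multiple imputation follows if data are missing at random (MAR). Pattern-mixture models and sensitivity analyses follow if data are found to be missing not at random (MNAR).

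**The concern.** The same app delivers the intervention and carries the outcome questionnaire. A patient who stops using it, or who is moved to another treatment before week 6, meets a listed end of participation and loses the only described means of giving the 6-week ISI. The weekly measures listed under Intervention do not include the ISI, so there is no interim value to fall back on.

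These exits are treatment experiences, so they plausibly relate to how the patient's insomnia is going. Facilitation is meant to help providers use the platform, so it could also change who stays on it. The loss may therefore differ by arm as well as by outcome. The superiority and non-inferiority parts of hypothesis 2 both rest on this one measurement.

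The missing-data rule adds a second problem. It makes the choice of method, and whether any sensitivity analysis is done, depend on a determination that the data cannot provide.

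**Working it through.** **1. The passages side by side**

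- Follow-up at 3 and 12 months is timed from the end of treatment. Completion of the course, with the app no longer necessary, is a listed end of participation. Read literally, the scheduled ISI falls after the exit.
- Once a patient has left the provider's care, the app is off and the app battery cannot be completed.
- Detection at about week 1 plus a 4-week course ends near week 5. A short course could therefore meet the completion condition before a week-6 ISI is due.

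**2. Reproducing the plan's detectable difference**

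Inputs from the Statistical analyses section: an average of 12 providers per group, m = 36 patients each, alpha 0.05 (taken as two-sided), power 0.80. The intra-class correlation of 0.01 is stated there for non-inferiority and is assumed here for superiority too.

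- Design effect = 1 + (36 − 1) × 0.01 = 1.35.
- SE = √[1.35 × (1/432 + 1/432)] = 0.0791, where 432 = 12 × 36.
- With a noncentral t on 22 df, the detectable d is 0.2318 and power at 0.232 is 0.801.

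The plan's figure reproduces, with every enrolled patient contributing. No patient dropout allowance is stated. With the actual 8 versus 16 split, power at 0.232 before any loss is 0.790 (normal) or 0.753 (t on 22 df), so the 12-versus-12 figures below are the favorable case.

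**3. With loss of 6-week ISI**

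The documents give no rate, so the range is assumed: equal loss per provider and nothing recovered by imputation. Replace m by 36 × (1 − loss).

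| Loss | m | Detectable d | Power at 0.232 |
|---|---|---|---|
| 0% | 36.0 | 0.232 | 0.80 |
| 10% | 32.4 | 0.241 | 0.77 |
| 20% | 28.8 | 0.252 | 0.73 |
| 30% | 25.2 | 0.266 | 0.69 |
| 40% | 21.6 | 0.283 | 0.63 |

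Non-inferiority power (8 versus 8 providers, margin 0.50, normal approximation) is 0.999 with no loss and 0.989 at 40% loss. Precision is not the problem there.

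**4. Direction and size of bias, for illustration only**

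If completers improve D standard deviations (SD) more than stoppers in every arm, a completer mean is too high by D × (proportion missing). The COAST+ minus COAST-only contrast then shifts by D × (missing in COAST+ − missing in COAST-only). With D = 0.5 and stopping of 20% versus 35%, all assumed, the shift is 0.5 × (0.20 − 0.35) = −0.075 SD. That is 0.075/0.232 = 32% of the detectable difference, and it understates the COAST+ benefit. With D from 0.3 to 0.8 and a gap in stopping of 0.10 to 0.20, the shift runs from −0.03 to −0.16 SD. The sign reverses if stopping is more frequent in COAST+, or if those who stop have improved more.

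**5. The missing-data rule**

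MAR and MNAR differ only in whether missingness depends on the unobserved values, given the observed ones. Any observed dataset is compatible with both. The condition that triggers pattern-mixture models and sensitivity analyses therefore cannot be established from the data.

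**The case against.** Several stronger readings are tempting, and the documents do not support them.

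- *A reader might infer that nearly everyone loses the 3- and 12-month ISI, and that those left are mostly non-remitters.* Switch-off depends on leaving the provider's care, not on finishing the sleep course, and the completion condition also requires that the app be no longer necessary. The providers treat comorbid conditions, so care may continue. The secondary analyses expect discharge at varying times after week 6. No share can be computed.
- *A reader might infer that this loss undermines the main hypotheses.* The 3- and 12-month points in hypothesis 1 are provider-level, hypothesis 2 uses 6 weeks, and the durability analysis uses ISI at discharge. No stated hypothesis test uses the 3- or 12-month ISI.
- *A reader might infer a completer-only primary analysis, or a bias toward COAST+.* The plan imputes missing outcomes and also fits a mixed model that can keep patients with baseline ISI only. The illustrated bias is that of a completer contrast, and it runs against COAST+.

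It can also be said that the exit wording sets the earliest point of termination without stating that data collection stops, and that a condensed article may leave post-discontinuation follow-up to the full protocol. That is fair, and another route may exist there. It does not remove the conflict between the two sections as published. Nor can imputation stand in for data that nobody is asked to provide: it would rest on baseline and early weekly measures and an untestable assumption. Leaving the ordering of missing-data methods to an analysis plan would be normal, but this article states a decision rule, and the rule does not work.

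**Conclusion.** The point holds in a limited form. The Intervention and Outcome measures sections conflict over ISI collection and must be reconciled. The consequence that matters is for the 6-week ISI: patients who stop or are referred early have no stated route to it, the loss is plausibly related to outcome and arm, and the sample size carries no allowance for it. The power loss to about 0.73–0.63 rests on an assumed 20–40% unrecovered loss, and the 0.075 SD shift on assumed stopping rates and an assumed difference in improvement. The risk to the 3- and 12-month ISI is real for patients who have left care, but of unknown extent and without effect on a stated hypothesis test. The mechanism-triggered missing-data rule is wrong as written, whatever the amount of missing data.

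**What to change.** **Collection.** Distinguish stopping the app or leaving care from withdrawing from the study. Leave the treatment and app-disabling rules as they are. Ask every consented patient who has not withdrawn to complete the ISI at a fixed 6 weeks from start, and at 3 and 12 months, by a questionnaire-only route clearly labelled as not monitored care. The label respects the protocol's reason for switching the app off, which is to avoid suggesting that a provider is still watching.

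**Analysis.** Drop the mechanism trigger. Make multiple imputation under MAR always primary, respecting clustering by provider and using the weekly measures already collected. Always report a delta-adjusted pattern-mixture sensitivity analysis. State an expected loss of 6-week ISI and show power with it. Label any bias illustration as an assumption and give its direction.

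**Cost.** The collection change needs a consent and ethics amendment, reminders, and a contact route, because the article says that no identifiable information is collected through the app or portal. The analysis change is wording only. The collection change should come first, since an ISI that was never collected cannot be recovered later.
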